As a primary outcome, buprenorphine *uptake* is defined as a pharmacy pickup and taking the prescription one or more times during the study period. Buprenorphine *adherence* is indicated by more than one buprenorphine positive screens taken at the library or at FJV Health Center and ideally continuing to take buprenorphine as prescribed for eight or more weeks. The rationale for the primary outcomes, buprenorphine uptake and adherence, via weekly drug screening, is to try to capture the patterns of buprenorphine uptake and adherence among unhoused populations, a likely more isolated and neglected group when it comes to finding, starting, and adhering to buprenorphine due to being unhoused. Therefore, we measure adherence as a primary outcome with 1 + buprenorphine positive tests, ideally for 8 + weeks of 12 weeks (3 months), rather than the standard 3–12 months adherence.

In the study’s formative stages of intervention development, study staff conducted interviews and focus groups with library patrons (those experiencing homelessness or living in a shelter or treatment program), library staff (i.e., security personnel, librarians, outreach workers), general public/parents, and buprenorphine providers to get reactions to the proposed program and to inform the study design. For example, five focus groups with library patrons were conducted across four libraries in San Diego to assess the potential feasibility and acceptability of the planned intervention. The findings from these interviews and focus groups inform the design of the telehealth intervention at the libraries and the measures that can be used in a randomized controlled trial. For example, we gained insights for recruiting and screening participants for opioids (being discreet in public spaces), enrollment procedures (coordinating with medical providers), and timing of the randomization (after first buprenorphine medical provider visit). Another recommendation made is to have persons with lived experience, especially with substance use recovery and experiences with buprenorphine, on the team. Focus group participants suggested recruitment strategies such as placing flyers at specific library bulletin boards frequently visited by unhoused individuals, which many identify as providing a consistent and reliable source of community information.

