### Pilot study design

This multisite study employs a parallel-arm randomized controlled trial design with participants allocated to library-facilitated telehealth visits for buprenorphine treatment (BBB intervention) or standard-of-care clinic-based or telephone visits (control). Participants are interviewed before randomization (baseline) and surveyed again at 1-, 2-, 4-, 8-, and 12-weeks (follow-up) to assess participant characteristics and study outcomes.

The study staff also conducts weekly urine drug screenings in the libraries with participants in both study arms to assess buprenorphine uptake and potential continued use of other drugs including fentanyl and other opioids. However, these additional urine drug screening and weekly follow ups at the library are not part of the usual clinic care or telehealth treatment procedures; instead, the clinic already requires in-person urinary drug screenings. Therefore, the additional library-based drug screenings occur to promote study engagement and retention in the study assessments, and to track outcomes without sole reliance on clinic record data. We also collect medical record and pharmacy pick-up data (via the CURES database described below) as part of the study design. Although these procedures are carefully determined to ensure rigor in the evaluation design, participating in these procedures is not a requirement for the library telehealth intervention itself. Participants can continue to use library telehealth without the need for weekly drug screenings in the library upon completion of the study.

Institutional Review Boards at San Diego State University and the University of California San Diego approved this study.

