### Intervention condition

In the intervention group, participants are scheduled for regular appointments at the FJV Health Center, which they attend via telehealth at the library. However, they can also access telehealth with FJV Health Center at unscheduled times. Unscheduled drop-in appointments is a standard available option for FJV Health Center patients and can be extended to library telehealth. The ability of unhoused participants to keep their regular buprenorphine appointments, whether in-person or by library telehealth, is a process measure for the study.

In some situations, participants can be interviewed outside of the library, if a room is not available in the library or the participant has too many belongings to bring inside the library.

Efforts are made to keep appointments private in locations not within hearing distance of others. The libraries have a computer tablet on a telehealth floor stand in a private study room for this study. The libraries make the computer tablet available on a heavy platform (to prevent theft) that can be placed in a library study room. The tablet is an alternative that removes barriers for patrons without ID cards who would otherwise need an ID card to check out library laptops.

FJV medical providers follow standard of care practice (whether in-person visit or over telehealth) to provide medication adherence counseling, medication education (e.g., how to take buprenorphine), information about what to expect, appointments, and treatment goals (e.g., relapse prevention, health/mental health referrals). Researchers help make follow-up appointments with the FJV Health Center for both the control and telehealth library groups, and research or library staff can also assist patrons with logging on to their telehealth appointments.

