As part of usual care for participants in both study arms, participants are still expected to attend the FJV Health Center in-person when asked to do a follow-up urinary drug assessment at the clinic, despite participating in the drug screenings weekly at the library. Participants in the library-facilitated telehealth arm are not forced to use the telehealth option solely; they can still attend in-person medical visits (provide clinic urine samples), Alcohol and Drug (AOD) counselor visits, and support groups at the clinic. Therefore, the continued in-person visits to the clinic and uptake of library telehealth is another process measure. As described below, the control group is only offered library-facilitated telehealth once they complete their 12-week study participation.

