### Data collection

#### Baseline and longitudinal assessments/measures

Following a FJV Health Center physician’s buprenorphine prescription, research staff track the participants’ buprenorphine medication uptake (pharmacy pickup, taking prescription one or more times during the first two weeks in the study), adherence (more than one buprenorphine positive screen), and medical appointment keeping through urinary drug screenings, interviews conducted at public libraries, and medical record data. All participants are invited to return to the library weekly for urinary drug screenings and to complete follow-up survey assessments at weeks 1, 2, 4, 8, and 12. Baseline and follow-up assessments are conducted in reserved library study rooms or conference rooms.

The 60-minute baseline survey captures the following domains: sociodemographic, behavioral, social supports, telehealth utilization and comfort, library usage, substance use behaviors, overdose experiences, and treatment history, along with the biomarker and medical record data collection (see Table 2). The content of the follow-up surveys is the same as the baseline surveys except that participant history and demographics are removed. The follow-up survey is shorter (30 min), retaining questions surrounding buprenorphine uptake, healthcare utilization, and barriers and facilitators to use. Follow-up questions also ask participants to recall experiences since their last visit with the research team in the library, particularly to determine the feasibility and acceptability of the library telehealth intervention; ease and understanding of being in the randomized controlled trial; experiences following up with the medical provider whether in-person or by telehealth; and their experiences with picking up and taking the buprenorphine medication.

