**Primary Outcomes**		
Buprenorphine uptake and adherence	Biomarkers: urinary drug assessments at the library and clinic. Pharmacy pickups of buprenorphine Self report: “How often do you take it? What is the dosage? Are you taking it correctly (as prescribed)? If not, why?” “Did you run out of your prescription before getting a refill?” “Have you stopped taking buprenorphine?”	Study generated Uptake: the proportion of people who pick up from the pharmacy and take buprenorphine 1 or more times at initiation, i.e., during the first 2 weeks, confirmed by biomarkers (urinary drug screens at the library and clinic, pharmacy pickup data from the state’s CURES database) Adherence = more than one buprenorphine positive screen taken at the library or at the FJV Health Center, ideally for 8 + weeks.

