### Strengths and limitations of the study design

Having drop-in clinic appointments available in both the telehealth library and in-person clinic control conditions is both a strength and limitation of the study. Drop-in appointments are a low barrier feature of the federally qualified healthcare center’s protocol that works well for unhoused patients. However, if a clinic setting does not allow drop-in clinic appointments, the implications are that a social worker in the library or health navigator will be even more necessary in real-world clinical practice to ensure patrons make and navigate their appointments on time. Usually, an appointment is made, but the clinic allows patients to see the medical provider within the block of time (i.e., morning or afternoon). If they do not show up at their appointment time, they can still see the medical provider within that morning or afternoon shift. Or, they can drop-in any other day on a first-come, first-serve basis. Generalizability is further limited by the requirement to have in-person visits for the first visit, though even during the COVID-19 pandemic when visits were mostly virtual, visits for in-person urine drug screenings were still required by FJV and other health centers.

Furthermore, if the rationale for the library-based intervention is to increase access to treatment, the frequency of urine tests and research assessments in this pilot study is greater than what is typically required in contemporary office-based buprenorphine treatment in many areasof the country. For this study, we want to have frequent follow-ups to ensure a higher likelihood of follow up to retain participants in the study protocols (surveys, interviews). However, an unintended consequence might be that participants will retain on buprenorphine more just by being in frequent contact with study staff. However, because we follow up weekly with all participants, regardless of the treatment vs. control condition, it does not impact our comparisons between conditions. An implication might be that having staff such as library social workers interacting with participants is important in carrying out such an intervention.

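### The adherence outcome rises with the number of urine screens taken, which may differ by arm, so equal weekly follow-up does not by itself protect the comparison

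*Protocol article*

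**What the plan says.** The section headed Feasibility of RCT to evaluate the current intervention says that adherence is "indicated by more than one buprenorphine positive screens taken at the library or at FJV Health Center", ideally with continued use for eight or more weeks. The primary-outcome rows of Table 2 repeat the rule. The same feasibility section also puts it more loosely: "we measure adherence as a primary outcome with 1 + buprenorphine positive tests, ideally for 8 + weeks of 12 weeks (3 months". Under Sample size and planned data analyses, the denominator for uptake and adherence is the number of people prescribed, not the number of screens due or taken.

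Screens come from two places. Under Pilot study design, staff run screens at the library: the study "conducts weekly urine drug screenings in the libraries with participants in both study arms". Attendance is voluntary, as Baseline and longitudinal assessments/measures states: "All participants are invited to return to the library weekly for urinary drug screenings". The clinic tests urine as well. Under Intervention condition, as usual care in both arms, "participants are still expected to attend the FJV Health Center in-person when asked to do a follow-up urinary drug assessment at the clinic". No number of clinic screens is given.

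What is randomized is where follow-up care takes place. In the telehealth arm, "participants are scheduled for regular appointments at the FJV Health Center, which they attend via telehealth at the library". Control participants go to the clinic in person or, according to Pilot study design, may have telephone visits.

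Strengths and limitations of the study design raises the possibility that frequent staff contact keeps people on buprenorphine, and answers that "because we follow up weekly with all participants, regardless of the treatment vs. control condition, it does not impact our comparisons between conditions".

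**The concern.** A rule of at least two positives, with no fixed number of tests, measures testing as well as drug use. A screen not taken cannot be positive, and the person stays in the denominator. If one arm is tested more often, it will look more adherent even when true use is the same.

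The two places where urine is tested are also the two places between which the intervention moves participants. More presence at the library could raise library screens in the telehealth arm; more in-person clinic visits could raise clinic screens in the control arm. An equal weekly invitation fixes neither.

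At stake is an ascertainment artefact in a primary-outcome contrast. The article says that adherence estimates will support power calculations for an efficacy trial, so the artefact could carry forward into that design.

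**Working it through.** The article gives no positivity rate, no achieved number of screens and no figure on this point, so there is nothing to reproduce. All rates and counts below are assumptions. True use is set identical in both arms, so any difference is artefact.

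**1. The rule rises with the number of screens n.** With independent screens, each positive with probability p:

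P(at least 2 positives) = 1 − (1−p)^n − n·p·(1−p)^(n−1)

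At p = 0.3:
- n = 6: 1 − 0.118 − 0.303 = 58.0%
- n = 9: 1 − 0.040 − 0.156 = 80.4%

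That is a gap of 22 points. Under the looser one-or-more wording the probability rises too: at p = 0.2 it is 59.0% with 4 screens and 93.1% with 12.

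**2. Allowing for persistent users and non-users.** Independence within a person is unrealistic. Let each person's positivity follow a beta distribution with mean m and intraclass correlation ρ, so that α = m(1/ρ − 1) and β = (1 − m)(1/ρ − 1). The number of positives is then beta-binomial. Percent meeting the rule:

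| Mean m | ρ | 6 screens | 9 screens | Gap (points) |
|---|---|---|---|---|
| 0.3 | 0.3 | 47.1 | 57.7 | 10.6 |
| 0.3 | 0.5 | 41.8 | 48.4 | 6.6 |
| 0.5 | 0.3 | 72.8 | 81.8 | 8.9 |
| 0.5 | 0.5 | 65.1 | 71.6 | 6.5 |
| 0.7 | 0.3 | 89.6 | 94.3 | 4.6 |
| 0.7 | 0.5 | 83.2 | 87.5 | 4.3 |
| 0.8 | 0.3 | 94.8 | 97.4 | 2.6 |
| 0.8 | 0.5 | 90.1 | 93.0 | 2.9 |

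Gaps are taken before rounding. The artefact is about 7 to 11 points at 30–50% mean positivity and about 3 to 5 at 70–80%.

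**3. Direction.** Let each of 12 library weeks be attended with probability a, add m clinic screens, keep p common to both arms, and write q = a·p. With independent screens:

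P(at least 2) = 1 − (1−q)^12·(1−p)^m − [12q(1−q)^11·(1−p)^m + (1−q)^12·m·p·(1−p)^(m−1)]

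Telehealth versus control at p = 0.2, with the gap at p = 0.8 beside it:

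| Assumed pattern (telehealth / control) | Telehealth | Control | Gap at p = 0.2 | Gap at p = 0.8 |
|---|---|---|---|---|
| Library 50% / 50%, clinic 1 / 5 | 41.6% | 66.8% | −25 | −1 |
| Library 75% / 50%, clinic 1 / 1 | 61.7% | 41.6% | +20 | +1 |
| Library 75% / 50%, clinic 0 / 4 | 55.7% | 61.4% | −6 | 0 |
| Library 50% / 50%, clinic 2 / 2 | 48.8% | 48.8% | 0 | 0 |

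The sign depends on which site dominates, opposing differences partly cancel, and equal testing gives no artefact. These gaps assume independence, so step 2 is the better guide to size.

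**4. What scoring by week can and cannot do.** One result per study week, with untested weeks counted as not positive, removes repeat screens within a week. It leaves step 2 untouched: 9 against 6 tested weeks gives the same gaps, because the present rule already treats an untaken screen as not positive.

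**5. Scale.** With 20 per arm (1:1 assumed from the target of 40) and proportions near 50%, the 95% half-width for a difference is 1.96 × √(2 × 0.25/20) = 0.31, or 31 points.

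**The case against.** Much in the plan favours equal testing. Both arms have the same weekly library schedule, clinic urine requirement, outreach after missed visits, payments and transport passes. Nothing ties telehealth appointments to the two or three days a week when research staff are at the library. Control participants are recruited around the libraries, the Central Library is 0.4 miles from the clinic, and control visits may be by telephone. A reader might infer that the design gives the arms different numbers of screens, or that the bias favours telehealth. The documents support neither: they show only that the achieved number is not fixed and may differ.

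A reader might also take the sentence in Strengths and limitations as a false claim about ascertainment. In context it concerns the effect of staff contact on staying on treatment, and for planned contact the reasoning is fair. It is too broad only if carried over to the adherence outcome.

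On size, the 22-point gap needs independent weeks and 30% positivity. The realistic gaps are well inside the 31-point half-width, and the pilot is declared not powered for efficacy. That limits the weight of the point without removing it, since bias adds to imprecision.

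Finally, pharmacy pickups are already collected and listed with uptake and adherence in Table 2, and completion of follow-up will be reported. The written adherence rule, however, rests on screens, and rules for missed screens elsewhere would not change that definition.

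**Conclusion.** The point holds in a limited form. The adherence rule rises with the number of screens taken, pools two sites with no fixed number, and is applied in a trial that randomizes the place of care. Equal planned follow-up therefore does not establish equal opportunity to test positive, and the statement of no impact does not follow for adherence.

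The artefact is about 7 to 11 points at 30–50% mean positivity and about 3 to 5 at 70–80%. These figures rest on assumed identical use, an intraclass correlation of 0.3 to 0.5 and 6 versus 9 screens; none of these values is in the article. Direction is unknown, and with equal testing the artefact is zero.

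**What to change.** 1. Add a fill-based adherence measure for every randomized participant: the share of the 12 weeks covered by dispensed buprenorphine fills in CURES, analysed by arm beside the urine measure. It does not depend on attending screens, so it carries most of the correction. It assumes that fill dates and days supplied can be extracted; the article mentions only confirming pickups.
2. Score at most one urine result per study week, whichever site supplied it, and state that this does not remove differential attendance.
3. Report screens taken per participant by arm and site, and interpret the urine contrast with caution if they differ. A difference in sign between the urine and fill measures should not by itself discard the urine result, because with 40 participants signs can differ by chance.
4. Limit the sentence in Strengths and limitations to planned contact, and add that testing opportunity may differ by arm.

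The cost is wording, one derived variable and one table, from data sources already in the plan and with no new visits. The downsides are that extra clinic positives within a week no longer count, and that fills show possession of the drug rather than ingestion, which is why the urine measure stays beside them.

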#### Feasibility of the telehealth intervention

Proportion of telehealth intervention arm participants who complete at least one telehealth visit appointment at the library.Proportion of scheduled visits with the buprenorphine provider that participants attend via telehealth at the library.We will also document any barriers to telehealth that arise (e.g., internet connection issues).

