### Study materials and incentives

For each baseline and follow-up visit for library-facilitated telehealth and control arms, all participants completing assessments with the library researcher staff receive $20 cash (gift card optional), transportation day passes per library visit with the researcher, and snacks/drinks.

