Urinary drug assessments at the library are not part of the intervention, but rather part of the research assessment procedures and to better track participants over time (a strategy for reducing loss to follow up). Urinary drug assessments for buprenorphine are still required in-person at the clinic as the routine medical procedures for both arms of the study, a standard procedure even during the COVID-19 pandemic at FJV Health Center. The urinary strips at the library are dipsticks used to assess for buprenorphine, fentanyl, and other drugs to assess for the primary outcome of the study (buprenorphine uptake and adherence) and secondary outcome (reduction of fentanyl and other drugs). The participants use library bathroom facilities to collect their weekly self-administered urinary drug screening tests. Patrons take the urinary drug test strips (for buprenorphine, fentanyl, and other drugs) and a plastic cup to the library bathrooms and return the test strips in a clear hazard bag for the study staff to record in a de-identified log. After each visit with research staff, participants receive 20 dollars cash and a Metro Transit System pass(es) as reimbursement for their time and travel needs to and from their clinic or library appointments. As noted above, these urinary drug assessments in the library and incentives/compensation are not required or offered for the telehealth intervention in the library after the study ends. Only the library telehealth would still be available.

We anticipate that many participants do not have a cellular phone or reliable phone access as phones are often lost, stolen, or run out of minutes due to the individual’s economic vulnerabilities, which exposes them to theft from other individuals, lack of income to pay the bill, and “sweeps” or forcible displacement from law enforcement. For follow-ups, the research staff obtain alternate phone numbers and emails of other individuals who can locate the participant. However, participants will be provided with information on the days and times the research staff are at the library and can simply show up at those designated times (two or three days per week). Researchers also keep library staff and security informed of the study location within the library and times of researcher availability to facilitate follow-up meetings with participants.

**Table 2 Tab2:** Measures

Topic/Variable	Covariate Measure	Survey instrument/measure

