#### Sample size and planned data analyses

Our target sample size for the trial is 40 participants, although we allow for a maximum of 60 participants to account for attrition. The sample size will provide adequate precision for effect size estimates, though not statistically powered to assess efficacy on primary outcomes.

Buprenorphine uptake (the proportion who pick up and take buprenorphine at initiation, confirmed by CURES database pharmacy pickup records and urinary drug screenings) and adherence (taking buprenorphine > 1 time, ideally for 8 + weeks), medical appointment adherence (attended medical appointments for buprenorphine two or more times as confirmed by clinic medical record data) will be divided by the number prescribed and scheduled, respectively.

Adherence estimates from this study will also provide the basis for power calculations in the design of future efficacy trials. Quantitative data analysis will consist of univariate statistics to describe the entire study sample and by study arm, the prevalence of individual responses, and the prevalence of treatment uptake and adherence. We will conduct an intent-to-treat (i.e., per-randomization) analysis following CONSORT guidelines to explore potential differences between study arms on the outcomes. Specifically, we will use regression models testing each outcome separately (using the appropriate test depending on the outcome distribution, e.g., logistic regression with binary outcomes). These models will treat the intervention condition (library-facilitated telehealth intervention vs. treatment-as-usual control) as the exposure in unadjusted models.

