In addition, the twenty-dollar weekly incentive for the participants’ time doing follow-up assessments, although a moderate, non-coercive amount, may motivate their initial interest and retention in the study. However, the incentive should not have an effect on the uptake and retention of buprenorphine because participants do not receive any additional incentive for taking buprenorphine medication. The participants only receive incentives, including snacks/drinks and transportation passes, to compensate them for their time and travel to the study sites. Again, both the control and intervention group receive the same incentives. At the same time, incentives may be the key to engaging a hard-to-reach unhoused population into any kind of assistance in the first place.

Regarding treatment retention, pilot data would need to be interpreted with caution because social workers or library staff may not be available to assist the patrons with telehealth in the library afterwards or at other sites. However, overall, the study design attempts to enable library-facilitated telehealth to be sustained with minimal extra work for libraries and clinics. Some patrons might be able to do so more independently than others which would be interesting to study in itself. When planning for an efficacy trial, understanding determinants of successful implementation, including sustainability (and costs) of the treatment model will be taken into consideration for the full-scale trial.

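### Library telehealth feasibility is measured while library attendance is paid, and the statement that the incentive should not affect uptake and retention is not supported by the reasons given for it

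*Protocol article*

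**What the plan says.** Under Study materials and incentives, "all participants completing assessments with the library researcher staff receive $20 cash (gift card optional), transportation day passes per library visit with the researcher". Strengths and limitations describes this as "the twenty-dollar weekly incentive for the participants’ time doing follow-up assessments". The section on baseline and longitudinal assessments describes the passes as "Metro Transit System pass(es) as reimbursement for their time and travel needs to and from their clinic or library appointments", so they cover clinic travel as well.

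Intervention participants attend their scheduled medical appointments by telehealth at the library (Intervention condition). Controls are not offered this during their 12 weeks (Control condition).

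The first feasibility measure is the "Proportion of telehealth intervention arm participants who complete at least one telehealth visit appointment at the library". The second is the share of scheduled provider visits attended in that way. Neither distinguishes days with a paid research visit from other days.

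On payment, Strengths and limitations states that "the incentive should not have an effect on the uptake and retention of buprenorphine". Its first reason is that nothing extra is paid for taking the drug. It then adds that both arms receive the same incentives. The section on conceptualizing the intervention, having noted that both arms get bus passes, uses equal treatment of the arms as the ground for attributing outcomes to library telehealth. The assessments section says that "incentives/compensation are not required or offered for the telehealth intervention in the library after the study ends", and that library telehealth would remain. The analysis section labels the exposure "library-facilitated telehealth intervention vs. treatment-as-usual control".

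**The concern.** The amounts are equal by arm, but they are tied to attending a place that is the point of care in one arm only. Money that brings a person to the library makes a telehealth visit there easier to add. It does not do the same for a clinic visit. Equal payment therefore does not rule out an effect of payment that differs by arm, and the lack of a payment for taking the drug does not bear on this. The same section also concedes that incentives may be what draws this population into help at all, which sits badly with a statement of no effect.

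Feasibility is the overall objective, and the Objectives section expects most participants to use library telehealth as assigned. A high proportion would naturally be read as willingness to use the service that remains after the study. It would in fact have been observed with payments that the service will not carry. The effect estimates may also inform a powered trial (Timeline and dissemination plans), where a treatment-as-usual label would leave out the support that controls receive here.

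**Working it through.** The article gives no rate, effect size, alpha or power, so there is no figure of its own to reproduce. The check sets the sections side by side and adds simple arithmetic.

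**1. Size of the payment.** Inputs: $20 per visit, 12 weekly visits, one baseline visit.
- Weekly visits only: 12 × $20 = $240.
- With baseline: 13 × $20 = $260.
- If only baseline and the five survey visits (weeks 1, 2, 4, 8, 12) were paid: 6 × $20 = $120. The text points to weekly payment.

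All of it is for visits with the library research staff.

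**2. Where payment and care meet.**

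| | Intervention | Control |
|---|---|---|
| $20 and passes given at | Library | Library |
| Medical visits | Library telehealth; clinic optional | Clinic or telephone |
| Clinic urine screens | Yes | Yes |
| Passes usable for clinic travel | Yes | Yes |
| Cash after the study | No | No |
| Library telehealth after the study | Yes | Yes, on offer |

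The arms differ in one row, and that row is what gives a library payment a possible differential effect.

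**3. Could telehealth visits fall on paid days?** Research staff are at the libraries two or three days a week (assessments section), rooms are reserved for the study days (Study setting), and research or library staff can help with log-on (Intervention condition). Overlap is plausible. Unscheduled telehealth is also allowed, and no section says how often the two coincide.

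**4. Direction for the arm contrast.** Co-location would favour telehealth. Passes for clinic travel help the control relative to ordinary care, because the Background names transport as a barrier. The net sign cannot be derived. Distance matters: the clinic is 0.4 miles from Central and 7.6 miles from Mission Valley, so any co-location effect is probably smaller at Central.

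**5. Which outcomes are exposed.** The first medical visit is in person at the clinic before randomisation in both arms, so uptake should be less affected than adherence and appointment-keeping.

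**6. Precision.** Assume 40 participants split 20 and 20, with true proportions p between 0.3 and 0.7.
- One arm's proportion: 1.96 × √(p(1−p)/20) = 0.20 to 0.22.
- Difference between arms: 1.96 × √(2p(1−p)/20) = 0.28 to 0.31.
- One arm at one library, assuming 10 people, at p = 0.5: 1.96 × √(0.25/10) = 0.31.

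The pilot could not separate a modest payment effect from chance, so the matter has to be handled by wording and description and not by a test.

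**The case against.** The strongest reply is that payment is identical by randomised arm, so the contrast is internally valid. This stands: the trial validly estimates the effect of offering library telehealth when library attendance is paid.

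A reader might go further and infer that a control must make a separate, unpaid trip for care. The documents do not support that. Pilot study design allows telephone visits for controls, the passes cover clinic travel, both arms still go to the clinic for urine screens, and Central is a 10-minute walk from the clinic. At most, a clinic visit carries no cash of its own.

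It can also be said that much is disclosed already: incentives may motivate interest and retention in the study, they stop afterwards, staff contact may act as an intervention, and treatment-retention data need caution. That is so, but the caution concerns the availability of staff to assist. No section considers that the paid visits take place at the telehealth site.

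Finally, a same-day flag does not isolate payment, because a same-day visit may reflect staff help or a free room. This is correct and limits how the flag can be read. It does not remove its descriptive value.

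**Conclusion.** The concern holds in a limited form. The feasibility proportions apply to paid library attendance, and the neutrality sentence goes beyond what its two reasons can show. This is the firmer half and follows from the article's own text.

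For the arm contrast the conclusion is narrower. Any effect of co-location is of unknown size and direction and is limited by telephone visits and clinic passes. A reader might infer that the comparison is biased towards telehealth. Nothing in the document establishes this, and the effect could be nil. What needs correcting is the attribution to telehealth alone and the description of the comparator.

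The payment of up to $260 assumes that baseline and all 12 weekly visits are attended and paid. The document offers no figure for the share of telehealth visits on paid days. This is a low-cost improvement to interpretation and not a flaw in the randomisation.

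**What to change.** 1. In Strengths and limitations, replace the sentence that the incentive should not affect uptake and retention. In the section on conceptualizing the intervention, replace the matching attribution statement. Say instead that effect and feasibility estimates apply under paid library attendance and study-funded transport. Where the analysis section names the treatment-as-usual control, state that this arm also receives passes, weekly paid library contact and staff help with appointments.

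2. Flag each library telehealth visit as same-day or not same-day as a paid research visit. Report both feasibility proportions overall and again counting only visits not on a paid research day, with the denominators unchanged, by library. Label this a descriptive sensitivity figure, and state that same-day visits may also reflect staff help or room availability, so the difference is not the effect of payment. By library, show counts beside percentages because the numbers are small.

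Cost: revised wording and one derived variable. Library session dates are in the tracking sheet and appointment attendance is in the separate clinic-linked database (Data tracking and management), so the flag needs a link by participant and date by staff with access to both. The price is a second, probably lower, feasibility figure and a narrower claim. No payment, procedure or clinical care changes.
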